## Methods

### Design

The planned design of this pilot RCT includes two parallel groups on a 2:1 (cycling:stretching) allocation ratio with allocation concealment and assessor blinding. The design adheres to the Standard Protocol Items Recommendations for Interventional Trials (SPIRIT) [45], the Consolidated Standards of Reporting Trials (CONSORT) elements [46], and the World Health Organization Trial Registration Data Set Version 1.2.1 guidelines (http://www.who.int/ictrp/network/trds/en/) for clinical trials protocols. Ninety community-dwelling older adults with mild-to-moderate AD will be enrolled: 60 will be randomized to the 6-month intervention (20 to 50-minute moderate-intensity cycling, 3 times a week) and 30 will be assigned to attention control (20 to 50-minute stretching exercise, 3 times a week; Figure 1). Cognition will be assessed at baseline before randomization and at 3, 6, 9, and 12 months, while hippocampal volume will be measured by MRI at baseline before randomization and 6 and 12 months. All data collectors will be blinded to the group assignments. This study is approved by the University of Minnesota’s Institutional Review Board (IRB: #1306M35661). Informed consent will be obtained from all participants. In the event that participants could not consent for themselves, they will give assent while their families or friends, in the descending order of power of attorney, spouse, adult children, and significant others will provide surrogate consent.

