**Table 1 Tab1:** **Eligibility criteria**

Inclusion criteria:	Exclusion criteria:
a) Verified diagnosis of Alzheimer’s disease	a) Resting heart rate ≤50 or ≥100 beats/minute
b) Mini-Mental State Examination score 15 to 26	b) Neurologic disorders (for example, non-Alzheimer’s dementia or head trauma)
c) Clinical Dementia Rating scale score 0.5 to 2	c) Psychiatric disorders (for example, bipolar, schizophrenia, or major depression)
d) Community-dwelling	d) Alcohol or chemical dependency
e) Age 66 years and older	e) Contraindications to exercise
f) English-speaking	f) If volunteered for Magnetic Resonance Imaging, abnormal imaging findings
g) Verified exercise safety	g) New symptoms or diseases (for example, chest pain, thrombosis) that have not been evaluated by the primary care provider
h) If on Alzheimer’s drugs, stable on drugs more than one month	h) Abnormal findings from the symptom-limited cycle-ergometer test (for example, cardiac ischemia or arrhythmia, inability to cycle)

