Subjects who pass all four steps will be considered ‘tentatively enrolled’ if they are willing to undergo MRI with MRI safety verification in step 3 above, or ‘enrolled’ if they refuse to participate in MRI or without MRI safety clearance in step 3 above. Tentatively enrolled subjects will be further screened for MRI eligibility using the Volunteer Safety Screening questionnaire mandated by the Center for Magnetic Resonance Imaging, and undergo baseline MRI if deemed safe. Subjects whose scans meet the following criteria will be notified to pursue medical evaluation with their providers and excluded from the study: normal pressure hydrocephalus, brain tumor, subdural hematoma, significant post traumatic encephalomalacia, one or more large hemispheric infarctions. Subjects whose scans do not meet those MRI exclusion criteria will be formally enrolled in the study.The subject timeline is depicted in Figure 2. The actual date of enrollment of the first subject was 3 June 2014.

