#### Other outcomes

This pilot RCT will inform a future full-scale RCT about potential outcomes that might be more sensitive to aerobic-exercise intervention: discrete cognitive domains; exercise adherence; aerobic fitness; physical function; BPSD; and medical changes (Table 4). Discrete cognitive domains include attention, processing speed, executive function, memory, and language. Each domain will be measured using instruments established in the AD Centers’ Uniform Data Set. Attention will be measured with Wechsler Digit Span. Processing speed will be measured with Wechsler Digit Symbol and Trial Making Test (TMT) Part A. Executive function will be measured using TMT Part B, Executive Interview-25 (EXIT-25) [62], Behavioral Dyscontrol Scale (BDS) [63] and Executive Clock Drawing Test (CLOX) [64]. Memory will be measured with Wechsler Memory Scale-Revised Logical Memory Story A and B Immediate and Delayed Recalls. Language will be measured with Animal and Vegetable Verbal Fluency and Boston Naming Test [65]. Exercise adherence will be calculated as: 1) the percent of the attended sessions divided by 72 for each subject; and 2) the percent of the attended sessions in which a subject meets the session prescription divided by the total attended sessions. Aerobic fitness will be measured by the symptom-limited peak cycle-ergometer [51, 66] and shuttle-walk [67], and the 6-minute walk test [68], Physical function [69] will be measured by Short Physical Performance Battery (SPPB) [70], and Disability in AD (DAD) scale [71]. BPSD will be measured by the Neuropsychiatric Inventory-Caregiver (NPI-Q; [72, 73]), Alzheimer’s Mood Scale (AMS) [74], and Cornell Scale for Depression in Dementia (CSDD) [75]. Medical changes include changes in medical conditions, falls, medications, and health care service use and will be tracked at each exercise session. An RA will code medical changes in the previous 3 months at each data collection.

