#### Aim 1: determine the immediate effect of the cycling intervention on cognition in Alzheimer’s disease

The primary comparison for both hypotheses in Aim I will be a 2-sided test of the overall mean in a 1-way ANOVA with age stratum as the factor and the change in ADAS-Cog from baseline to 6 months as the response against the null hypothesis value of 3.2 points, which is the mean 6-month increase in ADAS-Cog in pooled placebo groups of AD drug RCTs (n = 534) [48]. Separate ANOVAs will be run for each randomization group. Because we stratified treatment assignment (by age) in the design of the study, it is important that we account for this in the analysis of the trial data in order to realize the improved power of this design. Missing values at 6 months will not be imputed by last-observation-carried-forward because this would bias the mean change toward zero. Further analysis will use an analysis of covariance (ANCOVA) to determine significant difference in ADAS-Cog between groups at 6 months after adjusting for other covariates, including baseline ADAS-Cog and age stratum as covariates. Other covariates and potential outcome variables at baseline (Table 4) will be screened for possible inclusion in the model if any are associated with ADAS-Cog at a *P* < .1 level.

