#### Aim 2: examine if the cycling intervention slows cognitive decline in Alzheimer’s disease from baseline to 12 months

Variables will be screened as in Aim I as possible covariates to be included in the longitudinal model to refine the analysis. Additionally, we will continue to document exercise participation after the intervention ends, so continued exercise may be correlated with cognition in months 9 and 12. It is speculated that cognitive decline will slow or plateau in the cycling group. Therefore, we expect change points may occur, which will be included in the model as appropriate. Mixed-effects models as described for the analysis of Aim I will be used to explore changes from baseline to 12 months to obtain the estimates needed to design a future full-scale RCT.

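### The P<.1 covariate screen for the further, between-group ANCOVA can cost precision and, read literally, can drop subjects who have no MRI

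*Protocol article*

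**What the plan says.** Under Statistical analyses, Aim 1, the primary comparison is a one-sample test of the 6-month change in each arm against 3.2 points. The ANCOVA comes after it: "Further analysis will use an analysis of covariance (ANCOVA) to determine significant difference in ADAS-Cog between groups at 6 months", with adjustment "including baseline ADAS-Cog and age stratum as covariates". The rule at issue follows: "Other covariates and potential outcome variables at baseline (Table 4) will be screened for possible inclusion in the model if any are associated with" the outcome scale, with P<.1 as the cut-off.

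The text does not say whether the association is with baseline or 6-month ADAS-Cog, or whether it is judged marginally or given baseline ADAS-Cog.

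The rule reaches further than the ANCOVA. The Aim 1 text on longitudinal modelling first describes a mixed model with group, time and their interaction. It then says that models with the covariates found in the ANCOVA, and their interactions, will be considered. Aim 2 repeats the screen: "Variables will be screened as in Aim I as possible covariates to be included in the longitudinal model to refine the analysis".

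Table 4 lists hippocampal, brain and ventricle volume at month 0, and the Design section confirms that "hippocampal volume will be measured by MRI at baseline before randomization and 6 and 12 months". MRI is nevertheless optional. The Table 1 criterion reads "If volunteered for Magnetic Resonance Imaging, abnormal imaging findings", and the enrollment section counts subjects as enrolled "if they refuse to participate in MRI or without MRI safety clearance in step 3 above".

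**The concern.** Two things can go wrong when this rule is followed as written.

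- **Overlapping tests.** About half the candidates are cognitive measures. They correlate with ADAS-Cog because they measure much the same thing. Under a marginal screen many would pass while adding little to baseline ADAS-Cog, and each costs a degree of freedom in a model of about 75 subjects.
- **MRI volumes.** They are missing by design for anyone who declined MRI or was not cleared. An ordinary complete-case fit with one such covariate drops all of those subjects. A mixed model's tolerance of missing outcomes does not bring back a subject whose baseline covariate is missing.

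At stake is the precision of the adjusted between-group estimates, in a trial whose Discussion already concedes low between-group power and whose Aim 2 models are meant to supply estimates for a full-scale trial. An estimate from MRI volunteers only would also describe a narrower population than the one randomised.

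**Working it through.** **Inputs.** From Sample size: SD 6.25, two-sided 0.05, 60 and 30 randomised, 50 and 25 completers (60 × 0.84 = 50.4; 30 × 0.84 = 25.2). The share of subjects with MRI is not stated, so I assume 90 down to 50%.

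**The plan's own figure.** One-sample t, n = 50, difference 2.5: noncentrality 2.5/6.25 × √50 = 2.83 on 49 df. Power is 79.2% (80.7% by the normal approximation), so the stated 80% reproduces.

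The Discussion gives between-group powers of 50% at 3.5 points and 80% at 5 points, without an SD. At SD 6.25, 50 versus 25 completers give 61.6% and 89.7%; 25 versus 25 would give 49.2% and 79.1%. I use 50 versus 25 below. That mismatch is a separate matter and does not affect the relative losses.

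**Number of candidates.** My count from Table 4, beyond the two fixed covariates: 3 MRI volumes, 12 cognitive tests, 3 fitness, 2 function, 3 behavioural, CDR and MMSE, 3 demographics, WTAR, 2 activity measures = 31. At P<.1, 31 pure-noise variables would yield 31 × 0.1 = 3.1 passes on average.

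**Cost of overlapping covariates.** The fixed model has 5 parameters (intercept, group, baseline ADAS-Cog, two for age stratum). Adding k covariates that explain nothing further inflates the SE by about √(69/(69 − k)), where 69 = 75 − 5 − 1:
- k = 3: √(69/66) = 1.02
- k = 10: √(69/59) = 1.08
- k = 17: √(69/52) = 1.15

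Simulations with 50 versus 25 subjects, 15 tests correlated 0.6 with a latent trait, 15 weak variables and no MRI loss gave:
- Marginal screen, first set of variances: 19.4 of 30 pass on average; SE 1.541 against 1.460, ratio 1.06; type I error 4.3% against 4.4%.
- Marginal screen, second set of variances: 17 of 30 pass; SE 1.79 against 1.55, ratio 1.15.
- Marginal screen, assumed ADAS-Cog reliability 0.80 to 0.95: SE from about 16% larger to about 7% smaller. The gain appears when the latent trait also predicts decline.
- Screen conditional on baseline ADAS-Cog: about 3 to 12 of 30 pass, depending on the set-up. With about 3 passing there was no SE loss.

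**Cost of losing non-MRI subjects.** SE = 6.25 × √(1/n₁ + 1/n₂), with two-sample noncentral t power at 5 points:

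| Assumed MRI share | n₁/n₂ | SE | Power at 5 points |
|---|---|---|---|
| all completers | 50/25 | 1.53 | 90% |
| 90% | 45/22 | 1.63 | 86% |
| 80% | 40/20 | 1.71 | 82% |
| 70% | 35/18 | 1.81 | 77% |
| 60% | 30/15 | 1.98 | 70% |
| 50% | 25/12 | 2.19 | 60% |

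This table gives no credit for variance that the MRI volume explains. To break even, the volume must explain a share of the residual variance equal to the share of subjects lost, for example 30% at a 70% MRI share, on top of baseline ADAS-Cog.

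**How often an MRI volume would enter.** Three unrelated volumes at P<.1 give 1 − 0.9³ = 27%. Simulation (1,500 runs per setting, 25 noise variables plus 3 volumes, complete cases) gave 24 to 28%. With an assumed correlation of −0.3 between the volumes and baseline ADAS-Cog, at least one entered in 77 to 94% of runs. Power at 5 points then fell from 87–89% under the fixed model to 78, 69 and 56% at MRI shares of 90, 70 and 50%. Type I error stayed at about 4 to 5% throughout. That is expected, because baseline MRI precedes randomisation and the MRI subset is therefore defined before allocation.

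**The case against.** The strongest replies are these.

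- **It is not the primary analysis.** Correct. The one-sample tests against 3.2 points do not use the screen.
- **Another randomised comparison exists.** A reader might infer that the ANCOVA is the only between-group comparison at 6 months. It is not: the Aim 1 mixed model over the first 6 months starts without screened covariates and loses nobody for lack of MRI. Screened covariates are only considered later. What stands is that the ANCOVA is the planned test of the 6-month score itself, and that the screen recurs in Aim 2.
- **MRI may not be eligible.** The Other outcomes section says its list will "inform a future full-scale RCT about potential outcomes that might be more sensitive to aerobic-exercise intervention", and that list leaves out brain volumes, which are the secondary outcome. The screening rule may have meant only that list. The pointer to Table 4 excludes nothing, however, so the text allows both readings and needs settling.
- **Inclusion is only possible, and complete-case fitting is assumed.** Both are fair. Nothing obliges the statistician to enter every passing variable, and the protocol does not say how a missing covariate is handled. Missing-value patterns are to be examined, so a drop in n need not go unnoticed.
- **The size is fragile.** Also fair. The overlap cost depends on an unstated choice of screen and in one set-up becomes a gain; the MRI cost depends on an unstated share.

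**Conclusion.** The concern holds as a weakness in a secondary analysis rule that the protocol itself states. Choosing from about 30 candidates by their association with ADAS-Cog, with about 75 completers, offers no dependable gain and two avoidable risks. Overlap may add about 5 to 16% to the SE if the screen is marginal, and little or nothing if it is conditional on baseline ADAS-Cog. If an MRI volume is eligible, enters, and the fit is complete-case, power at 5 points falls from 90% to between 86% and 60% for assumed MRI shares of 90 to 50%, before any credit for explained variance.

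The documents do not support reading this as inflated type I error, as a threat to the primary endpoint, or as certain loss of the non-MRI subjects.

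**What to change.** Replace the P<.1 screen with a covariate set named in advance: baseline ADAS-Cog, age stratum and, optionally, a few prognostic variables measured on all randomised subjects, such as screening MMSE and education. State that MRI volumes, and any other variable not collected on everyone, are not eligible. Use the same set in the Aim 2 models. If a screened model is still wanted, label it exploratory and say whether the screen is conditional on baseline ADAS-Cog.

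This changes wording only and needs no new data. The downside is a possible small loss of precision if a variable left off the list proves strongly prognostic.

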#### Aim 2: examine if the cycling intervention slows cognitive decline in Alzheimer’s disease from baseline to 12 months

Variables will be screened as in Aim I as possible covariates to be included in the longitudinal model to refine the analysis. Additionally, we will continue to document exercise participation after the intervention ends, so continued exercise may be correlated with cognition in months 9 and 12. It is speculated that cognitive decline will slow or plateau in the cycling group. Therefore, we expect change points may occur, which will be included in the model as appropriate. Mixed-effects models as described for the analysis of Aim I will be used to explore changes from baseline to 12 months to obtain the estimates needed to design a future full-scale RCT.

#### Aim 3: assess the effect of aerobic exercise on hippocampal volume over 12 months

Hippocampal volumes will be graphed individually to discern any recognizable patterns of change for the intervention and control subjects. The volumetric data will then be assessed from baseline to 6 and 12 months using a mixed-models analysis as in Aims 1 and 2 to determine if any indications of discernible changes in hippocampal volume were associated with the intervention. Findings will not only generate effect size estimate, but significantly inform the potential mechanism of aerobic-exercise effects in AD.

#### Additional analysis for other outcomes

Other outcomes, including discrete cognitive domains, exercise adherence, aerobic fitness, physical function, BPSD, and medical changes will be analyzed similarly to global cognition as described under Aim 3. Mixed-models analyses will be perform to identify any discernible changes over time.

### Ethics

This study protocol is approved by the University of Minnesota IRB and DSMB. Any subsequent changes or amendments to the protocol will be submitted to IRB and DSMB for approval. Initial consent takes place during step 2 in-person screening, and subsequent consent/assent will be conducted similarly before each 3-month data collection following the same procedure during initial consent. In the event that subjects suffered research-related injury, treatment will be available, including first aid, emergency treatment and follow-up care as needed. However, care for such injuries during and after the study period will be billed in the ordinary manner to the subjects and their insurance companies.

### Dissemination

Findings from the study will be disseminated through publications and presentations. Subjects and their family members will receive a copy of published main findings. Authorship will follow the established publication guidelines such as the International Committee of Medical Journal Editors. We do not intend to use professional writers. Access to the final trial data set will follow the guidelines of the National Institute on Aging of the National Institutes of Health.

## Discussion

A few factors affected how we designed and operationalized this pilot RCT. First, we chose to stratify by age because we suspect that the effect of the intervention may not be consistent across ages. For example, younger subjects may be more likely to complete all the exercise regimes and do so at a higher intensity. Without stratification, there is no guarantee that the distribution of ages will be similar between the cycling and control groups and substantial sampling variability could arise among the three age strata since the sample size for this study is not large. We could by chance end up with a large percentage of 85+ in one group (cycling or control). Stratification will reduce sampling variability by ensuring a similar distribution of age in the two groups.

Second, a historical control was used for constructing hypotheses instead of utilizing the comparisons between intervention and control groups due to the small sample size and lack of power. For example, using a two-sample *t*-test, the sample size of 90 gives us 50% power to detect a group difference in the change in ADAS-Cog scores from baseline to 6 months when the true difference between the two groups is 3.5 points. We will have 80% power to detect a difference when the true difference is 5 points.

Third, we had removed an initial plan of conducting consensus diagnosis of AD using subjects’ medical records. Obtaining medical records had been very difficult and time-consuming and created a bottleneck for subject screening. Providers have different rules about releasing medical records and subjects often have multiple records in different health systems, resulting in substantial delay for us to receive a subject’s medical records. In addition, existing medical records rarely contain the needed data for a consensus diagnosis.

In summary, this pilot RCT will address the critical gap in aerobic exercise efficacy in AD by testing a well-characterized cycling intervention and using MRI to assess the biological mechanisms of action of aerobic exercise. This study will provide a potential treatment that may increase physical function and quality of life and curb the prohibitive costs for the growing AD population, as well as reduce caregiver burden. Our study could be easily translated into an evidence-based guideline that both professionals and the lay public can use to engage older adults with AD in aerobic exercise. If results are not as expected, the study will provide important foundations to inform future research.

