### Sample size

The primary endpoint is the 6-month within-group change in the ADAS-Cog, compared with the mean increase of 3.2 points from pooled placebo groups in AD drug RCTs with a total sample size of 534 (assuming equal numbers of mild and moderate AD subjects) [48]. Power calculations were based on a one-sample *t-* test (2-sided) at the 0.05 level, using the pooled standard deviation (SD) = 6.25 from the same placebo groups in AD drug RCTs [48]. Sample size was further determined by factoring in 16% attrition, which was based on the attrition rates from our previous studies [19, 20], 12 to 41% attritions in AD drug RCTs [49], and 0 to 41% attritions in non-AD exercise RCTs [12]. As a result, we will enroll 90 subjects and randomize 60 to the cycling group and 30 to the control group. The power calculation is conservative as it does not account for the stratified randomized design (or equivalently assumes that there is no difference between the strata, see below).

If 50 subjects in the exercise group complete the 6-month measurement, then the study has 80% power to detect a difference of at least 2.5 points with a one-sample 2-sided *t*-test at the 0.05 level. That is, if cycling leads to a true mean increase in the ADAS-Cog of no more than 0.7 points, the study will have 80% power to detect a difference from the increase of 3.2 observed in placebo groups in AD drug RCTs. In our control group, if 25 complete the trial, then the expected half-width of the 95% confidence interval for the mean 6-month change in the control group is 2.4. Although there is little power to detect a difference between our controls and the placebo groups in AD drug RCTs, our trial will provide a valuable estimate of the intervention’s Hawthorne effect.

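### The Discussion understates the power of the randomised 6-month comparison: at SD 6.25 and 2:1 allocation it is about 62% at 3.5 points and 90% at 5 points, not 50% and 80%

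*Protocol article*

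**What the plan says.** The Sample size section of the Protocol article sets out the primary calculation. It says "Power calculations were based on a one-sample" t-test, two-sided at the 0.05 level, "using the pooled standard deviation (SD) = 6.25 from the same placebo groups in AD drug RCTs". On numbers it says "we will enroll 90 subjects and randomize 60 to the cycling group and 30 to the control group". It allows for 16% attrition and works with 50 completers in the cycling arm and 25 in the control arm. From these inputs it claims 80% power for a 2.5-point difference from the historical placebo increase of 3.2 points.

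The Discussion, as its second design factor, explains why the hypotheses are built on a historical control and not on the comparison of the two randomised arms: the sample is small and power is lacking. As an example it says that with a two-sample t-test "the sample size of 90 gives us 50% power to detect a group difference in the change in ADAS-Cog scores" at a true difference of 3.5 points. It then adds: "We will have 80% power to detect a difference when the true difference is 5 points". It gives no SD, alpha or number per arm for these two figures.

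**The concern.** The two power figures are the only numerical support for making the comparison with a historical value primary, and the between-arm comparison secondary. A reader will assume that they rest on the inputs of the Sample size section, since the article gives no others. On those inputs the randomised comparison has clearly more power than stated. The figures therefore overstate the weakness of the between-arm comparison, in the paragraph that justifies giving it second place. The trial is also meant to supply estimates for a future full-scale trial, and a planner who took over these figures would start from a wrong picture of what 90 subjects can show.

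**Working it through.** **Inputs.** From Sample size: SD 6.25, two-sided alpha 0.05, 60/30 randomised, 50/25 completers (60 × 0.84 = 50.4 and 30 × 0.84 = 25.2). From the Discussion: 50% power at 3.5 points and 80% at 5 points. Assumption: the SD and alpha of Sample size also apply to the two-sample test, because the article states no others.

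**Step 1: reproduce the one-sample figure.** Standard error = 6.25/√50 = 0.884. Noncentrality = 2.5/0.884 = 2.83 on 49 degrees of freedom. Power from the noncentral t is 79.2%, which agrees with the stated 80%. The control-arm confidence interval also fits: 1.96 × 6.25/√25 = 2.45, against a stated half-width of 2.4. So 6.25 is the SD behind the Sample size section.

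**Step 2: two-sample power with the planned allocation.** Standard error = 6.25 × √(1/n₁ + 1/n₂), noncentrality = difference/standard error, degrees of freedom = n₁ + n₂ − 2.

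| Arms | Standard error | Power at 2.5 | Power at 3.5 | Power at 5 | Difference for 80% power |
|---|---|---|---|---|---|
| 50/25 | 1.531 | 36.4% | 61.6% | 89.7% | 4.35 |
| 60/30 | 1.398 | 42.4% | 69.7% | 94.3% | 3.96 |
| Stated | not given | not given | 50% | 80% | 5 |

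The stated figures are low by 12 to 20 points at 3.5 and by 10 to 14 points at 5. The choice of t or normal distribution does not explain this: the normal approximation for 50/25 gives 62.8% and 90.4%.

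**Step 3: look for the source of the stated pair.** The two figures agree with each other: 5/3.5 = 1.429, and the theoretical ratio of the differences for 80% and 50% power is (1.96 + 0.84)/1.96 = 1.429. They therefore share one set of inputs. With 25 per arm and SD 6.25 the standard error is 6.25 × √(2/25) = 1.768. The noncentralities are 3.5/1.768 = 1.98 and 5/1.768 = 2.83 on 48 degrees of freedom, and power is 49% and 79%. Both lie within about one point of the stated values, as close as the one-sample 79.2% lies to its 80%. The number 25 is the protocol's own count of control completers.

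**Step 4: other ways to reach the pair.** An SD of about 7.2 with 50/25, or about 7.9 with 60/30, also gives 50% and 80%. So does SD 6.25 with about 57 completers in a 2:1 split, a loss of (90 − 57)/90 = 37%. The first two need an SD that appears nowhere in the article. The third contradicts the 16% attrition in Sample size.

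**The case against.** The strongest defence is that the figures are an illustration in the Discussion. They err on the cautious side and set no sample size, test or endpoint. The reason they illustrate also survives correction. At the 2.5 points on which the primary test is sized, the two-sample test has only about 36% power with 50/25 and 42% with 60/30. To reach 80% it needs 4.0 to 4.35 points, more than the whole 3.2-point placebo increase. All of this stands, and it limits the weight of the point. It does not make the stated figures right for a sample of 90 randomised 2:1.

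A reader might infer more than the article supports, in two ways.

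- **A hidden larger SD.** One could read the gap as a favourable SD for the one-sample test and a larger one, about 7.2 to 7.9, for the comparison that was not chosen. On that SD the primary power at 2.5 points would be 67% down to 59%. The inference fails because 25 per arm at the stated SD of 6.25 reproduces both figures. The article shows no larger SD, and its one-sample calculation checks out.
- **An abandoned randomised comparison.** The Statistical analyses section keeps a between-group ANCOVA at 6 months and mixed models with a treatment-by-time interaction, and Hypothesis 2 compares the arms over 12 months. Only the primary test uses the historical value.

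**Conclusion.** The two power figures in the Discussion are wrong for the trial as planned. At SD 6.25, two-sided 0.05 and 50/25 completers, power is about 62% at 3.5 points and about 90% at 5 points, and 80% is reached at about 4.35 points. If all 60 and 30 are measured, the values are about 70%, 94% and 4.0 points. This rests on taking the SD and alpha of Sample size for the two-sample test, with an equal SD in both arms.

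The likely cause is the use of 25 subjects in each arm. That is an inference from the arithmetic, since the Discussion does not state its numbers per arm. The case for a historical primary comparison is weaker than the article makes it, but it is not overturned. This is a correction to stated figures, not a defect that requires a change of design.

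**What to change.** In the Discussion, state the SD (6.25), alpha (two-sided 0.05) and completers per arm (50 and 25) for the two-sample calculation. Replace the two figures with about 62% power at 3.5 points, about 90% at 5 points, and 80% at about 4.35 points. Add that power at 2.5 points is about 36%, which supports the argument more directly than the present figures do. Leave the one-sample calculation in Sample size as it is.

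The cost is two or three sentences. The sample size, primary test and endpoint do not change.
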